## **5 STUDY OBJECTIVE**

The study objective is to assess the habitual toothbrushing performance and habits in students without relation to dentistry or psychology by means of video filming. Results from video assessment will be related to oral hygiene, several questionnaires on personality traits, body image and previous experiences with dentists and knowledge on oral hygiene. The primary purpose of this study is to explore current relationships and thereby to develop hypotheses for future research on oral health education.

## **6 INVESTIGATIONAL PLAN**

### **6.1 OVERALL STUDY DESIGN AND PLAN**

The study is a non-disguised, indirect, and structured observation study with healthy volunteers, no intervention other than the recording, classifying, counting and analysing of data takes place.

### **6.2 DISCUSSION OF THE STUDY DESIGN**

Volunteers in disguised observations tend to act more naturally and the data collected tends to reflect their true reactions. The primary concern with disguised observation however is the ethical concern over recording behavioural information that would normally be private or not voluntarily revealed to a researcher. Therefore, a non-disguised observation design was chosen. To overcome at least partly the disadvantages of a non-disguised observation, the filming was performed through a mirror so that the volunteers should feel less observed than with an obviously visible camera.

Contrary to expectations, however, filming appears to have limited influence on brushing performance. A study comparing video films from volunteers unaware or aware of being filmed revealed that there was no difference in brushing time and influenced performance only to a small extent (16). The assumption that the awareness of being filmed has little effects is also supported by the finding that in repeated video recordings the brushing performance of a volunteer showed a remarkable reproducibility (17). Mierau et al. (18) arrived at similar conclusions when assessing brushing habit patterns in the course of nine

sessions; variations in force, duration, and technique as well as in the sequence of brushing positions and number of changes of brushing sites were small.

Besides limitations due to the observational setting, it must be emphasised that the study population is limited in number and is not representative. Observed results need to be interpreted within these limitations.

### **6.3 STUDY CENTRES AND TECHNICAL REQUIREMENTS**

The study will be performed at the Department f. Zahn-, Mund- u. Kieferheilkunde, Klinik f. Zahnerhaltungskunde und Parodontologie and at the Klinik f. Psychosomatische Medizin u. Psychotherapie, both located at the Albert-Ludwigs-Universität.

The inclusion of volunteers and the clinical and observational procedures (video recording, plaque indexquestionnaires) and the data management will take place at the Department f. Zahn-, Mund- u. Kieferheilkunde, Klinik f. Zahnerhaltungskunde und Parodontologie. The analysis of the questionnaires at the Klinik f. Psychosomatische Medizin u. Psychotherapie. Data analysis will be primarily done at the Institut für Medizinische Biometrie und Statistik, minor analyses will also be done at the Department f. Zahn-, Mund- u. Kieferheilkunde, Klinik f. Zahnerhaltungskunde und Parodontologie and at the Klinik f. Psychosomatische Medizin u. Psychotherapie.

### **6.4 STUDY POPULATION**

Volunteers to be included are male and female volunteers living in Freiburg and studying at the University in Freiburg with no relation to dentistry and psychology. They will be recruited via advertisements at noticeboards at central points of the University. Group size is 170.

#### **6.4.1 Inclusion Criteria**

- Willing and able to give written informed consent
- Student at the University of Freiburg (at least 18 years of age)
- Not involved in dentistry (e.g. dental nurses or dental students) or in psychology (e.g. students in the field of psychology)
- Complete (including fixed dental restorations) and closed (except for extraction from orthodontic reasons) dental arches
- Sufficient German language skills
- Routine use of manual toothbrush

#### 6.4.2 Exclusion Criteria

- Fixed orthodontic appliances
- Removable dentures
- Mental or physical disability with the potential to influence oral hygiene
- Routine use of powered toothbrush

#### 6.4.3 Blinding

The video films will be analysed under blind conditions as to the questionnaires. This is achieved by retaining the respective parts of the CRF's until termination of the video assessments. The questionnaires will be analysed under blind conditions as to the video films.

### 7 FLOW CHART

|                                                                                                 |                                                                                        |
|-------------------------------------------------------------------------------------------------|----------------------------------------------------------------------------------------|
| Study protocol final version and Ethics Commission                                              |                                                                                        |
| after approval, recruitment of volunteers, volunteers receive appointment, at this appointment: |                                                                                        |
|                                                                                                 | inclusion/exclusion criteria, informed consent, inclusion of the volunteer             |
|                                                                                                 | plaque index                                                                           |
|                                                                                                 | supply of toothbrush                                                                   |
|                                                                                                 | video recording                                                                        |
|                                                                                                 | supply of questionnaires                                                               |
|                                                                                                 | payment of allowance                                                                   |
| after termination of the observation phase:                                                     |                                                                                        |
|                                                                                                 | assessment of video recordings                                                         |
| after termination of the assessment of video recordings:                                        |                                                                                        |
|                                                                                                 | transfer from source data to database (questionnaires and raw data of video recording) |
|                                                                                                 | statistical procedures                                                                 |

## 8 STUDY PARAMETERS

Parameters under study are:

### Clinical parameters

Plaque Index (PI) (18). The scores are: 0 – no plaque, 1 – plaque invisible but can be found with periodontal probe at the gingival margin, 2 – moderate plaque easily seen without probing, 3 – ample plaque easily seen. The PI is scored on two surfaces (that is buccal, oral) of all teeth without disclosing. An overall PI score is computed as suggested (18). Additionally, the maximum value per sextant is recorded and the percentage of surfaces showing a PI above 0.

### Toothbrushing parameters:

| Parameter                             | Description                                                                                                                      |
|---------------------------------------|----------------------------------------------------------------------------------------------------------------------------------|
| Handedness                            | Hand holding the toothbrush (left, right or both).                                                                               |
| Total brushing duration               | Time between the first contact of the toothbrush with teeth, and the last action of brushing.                                    |
| Effective brushing duration           | Total brushing duration without interruptions like rinsing, spitting or breaks.                                                  |
| Brushing strokes                      | Circling, horizontal-linear, vertical-linear, vertical-roll, jiggling (short horizontal) and unspecific brushing movements.      |
| Starting location                     | The first approached area (oral, vestibular, occlusal, and right side, left side or anterior) at the beginning of toothbrushing. |
| Brushing events                       | Frequency of alternations between the sextants, the tooth surfaces (oral, vestibular and occlusal) or a combination of both.     |
| TSI (Toothbrushing Systematics Index) | Analysis and calculation on the basis of the assessed brushing parameters                                                        |

### Questionnaires

- Socio-demographic data (according to Deutsche Mundgesundheitsstudie V (19))
- Toothbrushing education and toothbrushing habits (self-estimation, according to Deutsche Mundgesundheitsstudie V (19))
- Relation to oral hygiene and the own oral cavity
- Experience with dentists
- Dental related self-efficacy (20,21)
- General self-efficacy expectation (Allgemeine Selbstwirksamkeitserwartung (SWE), German version (22))
- Dental Anxiety Scale (original version (23); German version (24))
- NEO-five factors inventory (NEO Fünf-Faktoren-Inventar, NEO FFI (25))
- Dresden Body Image Inventory (Dresdner Körperbildfragebogen, DKB-35 (26))
- Prime MD Patient Health Questionnaire (PHQ, German Version PHQ-D (27), Questions to Depressive Symptoms and to Unspecified Symptoms of Anxiety)

## **9 PROCEDURES**

Volunteers are screened as to the inclusion/exclusion criteria and informed consent is obtained. At the same appointment, the PI is determined, afterwards the volunteers are asked to brush their teeth in their usual way standing/sitting in front of a mirror. Each volunteer is provided with a standard toothbrush. Brushing is performed without toothpaste to facilitate the assessment of the video recordings. While brushing, each volunteer is filmed through the mirror without the investigator present. The video film is saved on the computer with the volunteer's code as file name. After filming the questionnaires are delivered. After completion of the procedure the allowance is paid.

The video films are analyzed after termination of the observation phase. The data is directly transferred to an excel file, which represent the source data. The brushing duration is determined from the video display; the other parameters are obtained from visual judgment of the volunteer's behavior. The answers on the questionnaires are transferred to electronic files.

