| OBJECTIVE(S)                               | The study objective is to assess the habitual toothbrushing performance and habits in students without relation to dentistry or psychology by means of video filming. Results from video assessment will be related to oral hygiene, several questionnaires on personality traits, body image and previous experiences with dentists and knowledge on oral hygiene.
The primary purpose of this study is to explore current relationships and thereby to develop hypotheses for future research on oral health education |
| TREATMENT(S)                               | None                                                                                                                                                                                                                                                                                                                                                                                                                                                                                                                        |
| INCLUSION CRITERIA                         | Willing and able to give written informed consent
Student at the University of Freiburg (at least 18 years of age)
Not involved in dentistry (e.g. dental nurses or dental students) or in psychology (e.g. students in the field of psychology)
Complete (including fixed dental restorations) and closed (except for extraction from orthodontic reasons) dental arches
Sufficient German language skills
Routine use of manual toothbrush                                                                 |
| EXCLUSION CRITERIA                         | Fixed orthodontic appliances
Removable dentures
Mental or physical disability with the potential to influence oral hygiene
Routine use of powered toothbrush                                                                                                                                                                                                                                                                                                                                                       |

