|                             |                                                                                                                                                                                                                                                                                                                                                                                                                                                                                                                                                                                                                                                                                                                                                                            |                               |
|-----------------------------|----------------------------------------------------------------------------------------------------------------------------------------------------------------------------------------------------------------------------------------------------------------------------------------------------------------------------------------------------------------------------------------------------------------------------------------------------------------------------------------------------------------------------------------------------------------------------------------------------------------------------------------------------------------------------------------------------------------------------------------------------------------------------|-------------------------------|
| ENDPOINTS            | 
First endpoint:
correlation between TSI and sub-scores obtained from the questionnaires
 
Other endpoints:
Correlation between brushing performance (PI score) and the effective brushing duration, the frequency of alternations between brushing areas and TSI values
Analysis of the influence of personal efforts regarding maintenance of oral health (e.g. frequency of visits at the dentist, the frequency of brushing per day) on the brushing performance (PI) und the brushing systematics (TSI)
Correlation between the personal efforts regarding maintenance of oral health (e.g. frequency of visits at the dentist, the frequency of brushing per day) and the results of the DKB-35, the Neo-FFI and the PHQ-D.
 |                               |

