For interpreting results from oral hygiene studies, two basic points need to be considered. The first is the theoretical efficacy of tooth cleaning strategies, and it is obvious that the absence of plaque is related to the absence of plaque induced diseases i.e. gingivitis/periodontitis and caries. The second point is the practical efficacy of tooth cleaning strategies, the measure of which in the majority of studies is reduction of plaque levels. The latter, however, is a surrogate parameter as to research questions on oral hygiene techniques and its performance. Lack of reduction of plaque levels does not say anything about the practical efficacy of oral hygiene techniques, as long as nothing is known about the practical performance of oral hygiene, and the skills and dexterity of the included volunteers.

Interestingly, only few studies address these shortcomings of using plaque levels as a surrogate for brushing habits and investigate the brushing performance of volunteers by observing them during practicing the hygiene technique (5–10). These studies, however, have clearly shown that persons, being video-taped during their habitual toothbrushing, mostly brush more or less non-systematically and often do not reach all areas. Often the oral part of the mandible teeth is not brushed (10,11). In addition volunteers alter frequently between predefined areas, probably reducing the brushing efficacy in the respective area. A further very interesting outcome of these studies was that the inter-personally brushing habits show a wide variation; however, intra-personally the brushing habits are very constant or stable (12–14). The latter speaks for a deep rootedness of the movement patterns (15,16).

There are indications that a psychological intervention in combination with oral hygiene instructions can lead to an increase of brushing efficacy; however, the evidence is low (17). Furthermore, nothing is known about the relationship between personality traits (e.g. conscientiousness or neuroticism), body image (e.g. acceptance of one's body) and

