## **11 STATISTICAL METHODS AND DETERMINATION OF SAMPLE SIZE**

### **11.1 STATISTICAL ANALYSIS PLAN**

#### Definition of outcome measures and study objectives

Purpose of the study is to describe quality of current brushing behaviour in adults and thereby to identify needs for further dental education and to associate this with the outcome of the questionnaires to identify predictors for brushing habits.

In a first step the study population will be described with respect to socio-demographic and behavioural characteristics (brushing behaviour). The behavioural characteristics are the following:

- duration of tooth brushing (sec)
- starting location
- type of strokes per sextant
- number of movements between areas
- Toothbrushing systematics

From these data the TSI will be calculated.

In parallel, the information obtained from the questionnaires will be stored in MS-Access-Databases. The scoring of the questionnaires relies on MS-Access-Basic scripts which are already available at the Department of Psychosomatic Medicine and Psychotherapy. The scripts for DKB-35, NEO-FFI and PHQ-D were programmed according to published manuals or articles. These scripts were double checked and debugged. An equivalent procedure will be run for the Dental Anxiety Scale and the Dental Related Self-efficacy. All other forms (e.g. sociodemographic data) do not require standardized scoring procedures. All scores and descriptive data will be exported into a data table, which is compatible with common statistical analysis software (preferably MS-Excel, \*.xlsx).

The primary study aim is to correlate the individual brushing habits (effective brushing duration, frequency of alternations between brushing areas, TSI values) with the single scores and sub-scores obtained from the questionnaires.

Secondary objective is to correlate the brushing performance (PI score) with the effective brushing duration, the frequency of alternations between brushing areas and TSI values.

Furthermore the influence of personal efforts regarding maintenance of oral health (e.g. frequency of visits at the dentist, the frequency of brushing per day) on brushing performance (PI) and brushing systematics (TSI) will be analysed.

The third objective is to correlate the personal efforts regarding maintenance of oral health (e.g. frequency of visits at the dentist, the frequency of brushing per day) with the results of the DKB-35, the Neo-FFI and the PHQ-D.

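### The only plaque score is taken before the filmed brushing, with no rule on time since last cleaning, yet the secondary endpoints call it brushing performance

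*Protocol*

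**What the plan says.** **Order of measurement.** Protocol section 9 (Procedures): "At the same appointment, the PI is determined, afterwards the volunteers are asked to brush their teeth in their usual way". The flow chart in section 7 gives the same order, and neither place has a second PI after the filming.

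**How PI is scored.** Section 8, Clinical parameters: "The PI is scored on two surfaces (that is buccal, oral) of all teeth without disclosing". Sections 8 and 9 set no period without brushing before the visit, and section 8 does not list time since last cleaning as a parameter. Section 8 does list a self-report questionnaire on toothbrushing habits. Its items and the CRF are not shown.

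**What the endpoints call it.** Synopsis, Endpoints: "Correlation between brushing performance (PI score) and the effective brushing duration". Section 11.1: "Secondary objective is to correlate the brushing performance (PI score) with the effective brushing duration". Both go on to frequency of alternations and TSI, and both add the influence of personal efforts, such as brushing frequency per day, on PI.

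**What the same term means elsewhere.** The objective in the synopsis, repeated in section 5, is to "assess the habitual toothbrushing performance and habits in students without relation to dentistry or psychology by means of video filming". Oral hygiene is then a separate variable to which the video results are related. The introduction writes of "shortcomings of using plaque levels as a surrogate for brushing habits" and says that plaque reduction "is a surrogate parameter as to research questions on oral hygiene techniques and its performance".

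**The concern.** A plaque score taken before a brushing session carries no information on what that session removed. It combines plaque left by earlier brushing at home with plaque regrown since. If one volunteer arrives an hour after brushing and another the next morning, their scores differ for a reason unrelated to how they brush.

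Two things are at stake, both confined to the PI endpoints:

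- **Precision.** Differences in the interval that are unrelated to the filmed behaviour weaken the associations of PI with effective brushing duration, alternations and TSI. Each volunteer attends once, so an interval not asked about at that visit cannot be reliably recovered later.
- **Interpretation.** Under the present label, a correlation between PI and a video measure will be read as the efficacy of the brushing on film. The study does not measure that.

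**Working it through.** **1. The places that name or time the PI, side by side**

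| Place in protocol | PI or the term *brushing performance* |
|---|---|
| Sections 7 and 9 | PI first, then filmed brushing; no later PI |
| Synopsis (Endpoints) and 11.1 | brushing performance = PI score |
| Synopsis (Objective) and section 5 | performance is assessed by video; oral hygiene is a separate variable |
| Section 4 | performance is what observation reveals; plaque is a surrogate |
| Sections 8, 9 and 11 | no interval rule, no interval parameter, no interval in the analysis |

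One term thus names both sides of the secondary correlation: the pre-brushing score and the filmed behaviour it is correlated with.

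**2. The plan's own figure**

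Section 11.2 gives a TSI difference of 0.15, SD 0.3, α = 0.05 and β = 0.1. Taking α as two-sided, with two equal groups:

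n per group = 2 × (1.960 + 1.282)² × (0.3/0.15)² = 2 × 10.51 × 4 = 84.1, rounded up to 85; total 170.

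The stated 170 reproduces (power 0.903 at 85 per group). It rests on TSI alone, so nothing about PI alters it.

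**3. Illustration of the noise**

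The protocol gives no PI variance, so the following rests on assumptions. Let q be the share of PI variance due to the interval, and suppose that this part is unrelated to the video measure. Let r be the correlation of the video measure with the rest of PI. Then

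- r observed = r × √(1 − q)
- power = Φ( atanh(r observed) × √(n − 3) − 1.960 ), with n = 170 and √167 = 12.92.

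I take r = 0.25 because it is close to the correlation that 170 volunteers detect with 90% power: tanh(3.242/12.92) = 0.246.

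| q (assumed) | r observed | Power at n = 170 |
|---|---|---|
| 0 | 0.250 | 91% |
| 0.1 | 0.237 | 88% |
| 0.2 | 0.224 | 84% |
| 0.3 | 0.209 | 78% |
| 0.4 | 0.194 | 72% |

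For example, at q = 0.4: 0.25 × √0.6 = 0.194; atanh(0.194) = 0.196; 0.196 × 12.92 − 1.960 = 0.57; Φ(0.57) = 0.72.

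**4. Where adjustment helps and where it does not**

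- *PI against duration, alternations and TSI.* The chance part of the interval, such as when the appointment fell, is noise. Adjusting for it recovers precision.
- *Brushing frequency per day and PI.* People who brush more often tend to arrive with a shorter interval, and a shorter interval means less plaque. The interval therefore lies partly on the path from frequency to PI. Adjusting for it would remove part of the influence that section 11.1 sets out to describe.

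**The case against.** The best defence is that the target is habitual brushing. The introduction states that "intra-personally the brushing habits are very constant or stable", and section 6.2 reports that performance was reproducible across repeated recordings. On that premise, plaque found on arrival is a fair indicator of habitual plaque control, and the film samples the same habit. A score after filming would instead reflect one session with a supplied brush, no toothpaste and a camera. The protocol nowhere sets out to measure how well the filmed session cleaned. This stands. A reader might infer that the PI endpoints are invalid, and the documents do not support that. But stable habits justify a pre-brushing PI as a measure of oral hygiene status. They neither justify calling it brushing performance nor equalise the interval between volunteers.

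The introduction's criticism of plaque does not condemn the design either. It concerns plaque levels used when nothing is known about how people brush, and this study adds the film.

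Four further inferences are tempting and should not be drawn:

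- *The interval is not recorded.* The CRF and questionnaire items are not shown. One can say only that section 8 does not list it and the stated analysis does not use it.
- *The interval confounds the brushing-frequency analysis.* It is largely a mediator there, so making it a covariate in every PI model would be unsound.
- *Brushing performance is never related to personality.* That follows only from the label. The primary endpoint relates TSI to the questionnaire sub-scores, and section 11.1 adds duration and alternations. No extra PI-by-questionnaire endpoint is needed.
- *The study loses power.* The PI endpoints are not primary and are to be analysed descriptively. The power figures above only give a scale for the lost precision.

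**Conclusion.** The concern holds as a matter of labelling and avoidable noise. The only PI precedes the filmed brushing, the interval since last cleaning is left open, and the endpoints give PI a name that the protocol uses elsewhere for filmed behaviour.

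The effect is limited to secondary, descriptive associations in a study that calls itself exploratory. It weakens the PI-versus-video correlations without invalidating them. The primary TSI endpoint and n = 170 are untouched.

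The documents do not determine the size. The range of 88–72% power, against 91% without the noise, depends on three assumptions: an interval share of 10–40% of PI variance, a true correlation of 0.25, and an interval unrelated to the video measure.

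**What to change.** 1. **Record the interval.** Ask for hours since last toothbrushing before the PI is scored, or, if the CRF or habits questionnaire already has this item, name it in section 8.
2. **Use it selectively.** In section 11.1, adjust for it in the models relating PI to effective brushing duration, alternations and TSI. For brushing frequency per day and PI, keep the unadjusted result as the main one and show the adjusted result as a sensitivity analysis, because the interval is partly a mediator there.
3. **Relabel.** In the synopsis endpoints and section 11.1, call PI the pre-brushing plaque level (habitual oral hygiene status). Reserve brushing performance for the filmed measures.

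The cost is one question, one covariate in the PI-versus-video models, one sensitivity analysis and some wording. The question has to be in place before the volunteers' single visit. The answer is self-reported, so adjustment will remove only part of the noise.
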